Furthermore, previous studies have demonstrated a significant correlation between cognitive function and anhedonia (7, 26). Functional near-infrared spectroscopy (fNIRS) is a relatively non-invasive, well-tolerated, cost-effective optical neuroimaging tool. It can measure task-related changes in oxygenated hemoglobin and deoxygenated hemoglobin in the cerebral cortex (27), thereby revealing alterations in brain function, making it highly valuable for studying cognitive functions and brain activity (28). The Wisconsin Card Sorting Test (WCST) is a widely used neuropsychological assessment that reflects the function of executive decision-making areas in the frontal lobe and is employed to evaluate cognitive flexibility in both healthy and clinical populations (29). Studies have shown that individuals with schizophrenia perform worse on the WCST compared to the general population, indicating the presence of cognitive dysfunction related to executive functions in these patients (30, 31). Given that both fNIRS and the WCST provide complementary measures of cognitive function, we will utilize them to evaluate the cognitive functions of patients with anhedonia, aiming to explore whether improvements in anhedonia are associated with cognitive function.

This study aims to: (1) evaluate the efficacy and safety of DMPFC-iTBS for treating anhedonia in schizophrenia; (2) examine the relationship between anhedonia severity, prefrontal cortical activity, and cognitive performance; and (3) explore potential neurobiological mechanisms with the help of fNIRS.

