### Study design

2.1

This double-blind, randomized controlled trial will recruit 82 patients with schizophrenia and have a score of ≥12 on the Snaith–Hamilton Pleasure Scale (SHAPS) from the Zigong Affiliated Hospital of Southwest Medical University. Participants will be randomly assigned in a 1:1 ratio to receive either active or sham iTBS, with identical parameters and procedures aside from the stimulation condition. This study is conducted in compliance with the World Medical Association’s Code of Ethics (Declaration of Helsinki). All participants will be fully informed of the study protocol and will provide written informed consent.

Specifically, Individuals expressing interest in the program will first complete a screening questionnaire covering basic demographics and the SHAPS. Those who meet the preliminary inclusion criteria will be invited by their physician to participate. After providing written informed consent, eligible participants will undergo a comprehensive baseline assessment. This assessment includes the collection of clinical data, clinical scale evaluations, WCST, and an fNIRS scan. Following the baseline assessment, participants will be randomly assigned to either the active iTBS group or the sham stimulation group based on the number of randomization in the sealed envelope. The study comprises two phases: a treatment period (15 days) and a follow-up period (4 weeks). All participants in both groups will be evaluated using the SHAPS and the Scale for the Assessment of Negative Symptoms (SANS), and will undergo fNIRS scanning at three time points: before treatment (T0), immediately after treatment (T1), and 4 weeks after treatment completion (T2) (**Figure 1**).

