#### Sample size

2.7.1

This study focuses on the differences in outcomes due to the two populations at the three time points, and the statistical methodology lends itself to the use of repeated measures ANOVA. The dependent variable was set as the measurement outcome. The independent variables were between-groups for the rTMS group and sham rTMS group, and within-groups for the three time points of pre-treatment (T0), post-treatment (T1), and 4 weeks post-treatment (T2). The effect size used to calculate the effect size was 0.25, the significance level alpha was 0.05, the statistical test efficacy was 0.8, and the non-spherical corrected moderate deviation from the spherical hypothesis value was 0.75. We will need a sample size of 66 participants. If the maximum allowable dropout rate is 20%, the total sample size needed for this study would be 82 participants. The sample size calculation was carried out using G*Power version 3.1.9.7_143.

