#### Statistical considerations

2.7.2

Differences in demographic characteristics and clinical variables between the two groups will be compared using t-test for continuous variables and χ^2^ test for categorical variables. The primary and secondary outcomes will be analyzed using linear mixed-effects models, applied on an intention-to-treat basis. In addition, Pearson or Spearman correlations will be used to analyze the correlation of anhedonia with prefrontal activity and cognitive performance. All statistical analyses were performed using SPSS (Version 24.0; IBM Corp., Armonk, NY, USA).

To assess the integrity of blinding, participants were asked at the conclusion of the treatment period to guess their group assignment (active or sham). The distribution of guesses between the two groups was compared using a χ² test. A correct guess rate no better than chance (50%) in both groups would be considered evidence of successful blinding.

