## Discussion

3

The design of this protocol is based on the following key evidence. Recent studies have shown that rTMS targeting the DMPFC can alleviate anhedonia in depression by improving connectivity within the reward circuitry (15, 35). Anhedonia is a symptom of apathy in schizophrenia, but it is also a core symptom of depression. Some perspectives suggest that the overlap between anhedonia and apathy in schizophrenia can be explained by specific deficits in anticipatory pleasure, while consummatory pleasure experience remains relatively intact (36, 37). The mechanisms underlying anhedonia differ between schizophrenia and depression. As reviewed by Bégue et al., anhedonia in schizophrenia is associated with abnormalities in the prefrontal-striatal network, particularly involving the ventral striatum (VS), ventromedial prefrontal cortex (VMPFC), dorsolateral prefrontal cortex (DLPFC), and anterior cingulate cortex (ACC). Although DMPFC-iTBS has been explored in depression, its application in schizophrenia remains underexplored, representing an innovative strategy for targeting the complex network underlying anhedonia in this disorder (38). Furthermore, previous clinical studies have demonstrated the efficacy of DMPFC-targeted rTMS in schizophrenia with negative symptoms (39). We anticipate that the rTMS intervention in this study will lead to significant improvements in anhedonia among schizophrenia.

Anhedonia is associated with multiple reward processing components, including reward evaluation, anticipation, decision-making, and motivation (40). It is thought to potentially arise from dysfunction in the mesolimbic dopamine pathway and its terminal regions (e.g., striatum, amygdala, and prefrontal cortex) (41). It is noteworthy that these brain regions may also be involved in motivational processing (42), suggesting a possible shared pathological basis between anhedonia and amotivation in schizophrenia. The DMPFC, as a key node within the mesolimbic dopaminergic system (14), may be a promising target for rTMS to ameliorate anhedonia in schizophrenia.

To elucidate the potential neurobiological mechanisms of action, our trial collected cognition-related data, such as prefrontal cortex oxyhemoglobin levels measured via fNIRS. If analyses reveal correlations between improvements in anhedonia and these cognitive metrics, it could offer clues for further explaining the intervention mechanisms of rTMS.

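### The correlations meant to shed light on mechanism carry no term for arm; if the arms are pooled on change or post-treatment scores, a treatment effect on both measures creates a correlation by itself

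*Protocol article*

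**What the plan says.** The association analysis is one sentence in section 2.7.2: "Pearson or Spearman correlations will be used to analyze the correlation of anhedonia with prefrontal activity and cognitive performance". It follows the statement that primary and secondary outcomes go into linear mixed-effects models, so the correlations are an addition to those models. The sentence does not say which time point is used, whether levels or changes are correlated, or whether the arms are pooled, separated or adjusted for.

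The analysis serves the second and third aims in the Introduction: "examine the relationship between anhedonia severity, prefrontal cortical activity, and cognitive performance; and (3) explore potential neurobiological mechanisms with the help of fNIRS".

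The Discussion shows how the result would be used: "If analyses reveal correlations between improvements in anhedonia and these cognitive metrics, it could offer clues for further explaining the intervention mechanisms of rTMS".

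The design in section 2.1 has two equal arms: "Participants will be randomly assigned in a 1:1 ratio to receive either active or sham iTBS".

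**The concern.** Pearson and Spearman coefficients are bivariate and have no place for arm. The Discussion speaks of improvements, which are change scores, and in a randomised trial change scores carry the difference between arms. If active stimulation lowers SHAPS and separately shifts an fNIRS or WCST measure, the two arms form two displaced clouds of points. A coefficient through the combined cloud is then non-zero, even if patients with a larger marker change are no more likely than others in the same arm to have a larger SHAPS change.

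Such a coefficient repeats what the mixed models already test, namely that treatment moved both measures. It does not show that the two changes are linked within patients, which is what a clue to mechanism requires. The stake is the mechanism reading under the third aim, and the second aim to the extent that it is answered with post-treatment or change data.

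**Working it through.** **Inputs.** Two arms at 1:1 (section 2.1). Evaluable N = 66, planned total 82, effect size 0.25, alpha 0.05, power 0.8 and nonsphericity correction 0.75 (section 2.7.1). A cited meta-analysis of non-invasive brain stimulation gives an SMD of 0.63 in size for anhedonia (Introduction); it serves here only as a value in the range. The article gives no effect for fNIRS or WCST and no within-subject correlation ρ.

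**Step 1: the plan's own figure.** The article states no figure for the correlation analysis, so the sample size is the only one to reproduce. For the within or within-between effect with 2 groups and 3 measurements, λ = f²·N·m·ε/(1−ρ). With ρ = 0, λ = 0.0625 × 66 × 3 × 0.75 = 9.28 on 1.5 and 96 degrees of freedom. Power is 0.809, and 66 is the smallest even N that reaches 0.8. With ρ = 0.5 the same formula gives 34. So the stated 66 goes with ρ = 0.

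**Step 2: the effect implied on change scores.** Two readings of f = 0.25 are possible.

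- Two groups at one time point: d = 2f = 0.5.
- An interaction in which the arms differ by 0, Δ, Δ at T0, T1, T2. The interaction terms are ±Δ/3, Δ/6, Δ/6 in size, so f² = Δ²(1/9 + 1/36 + 1/36)/3 = Δ²/18, and Δ = 0.25 × √18 = 1.06 in raw-score SD. The SD of a change score is √(2(1−ρ)) raw SD. At ρ = 0 this is 1.414, so the effect is 1.06/1.414 = 0.75 change-score SD.

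**Step 3: the induced correlation.** Let the within-arm correlation be zero, and let the arms differ by d₁ and d₂ within-arm SD on the two change scores. At 1:1 allocation,

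r = (d₁d₂/4) / √[(1 + d₁²/4)(1 + d₂²/4)].

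For d₁ = d₂ = 0.75: 0.1406/1.1406 = 0.123. For 0.63 on both: 0.0992/1.0992 = 0.090. For 0.5 on both: 0.0625/1.0625 = 0.059. If either effect is 0, r = 0.

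**Step 4: how often the pooled Pearson test rejects.** Simulation with normal data, two-sided 0.05 and 40,000 to 60,000 replicates per row:

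| SHAPS effect (SD) | Marker effect (SD) | Induced r | Pooled, N = 66 | Pooled, N = 82 |
|---|---|---|---|---|
| 0.5 | 0 | 0 | 5.1% | 4.9% |
| 0.63 | 0.3 | 0.04 | 6.4% | not run |
| 0.75 | 0.3 | 0.05 | 7.2% | not run |
| 0.5 | 0.5 | 0.06 | 7.6% | 8.0% |
| 0.63 | 0.5 | 0.07 | 9.0% | 10.0% |
| 0.63 | 0.63 | 0.09 | 11.0% | 12.7% |
| 0.75 | 0.75 | 0.12 | 17% | 20% |

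A check by Fisher's z for the last row at N = 66: atanh(0.123) × √63 = 0.98, and P(Z > 1.96 − 0.98) + P(Z < −1.96 − 0.98) is about 0.17, in agreement.

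**Step 5: adjusting for arm.** The partial correlation given arm averages about 0 and rejected in 4.8% to 5.2% of replicates wherever it was run, at both sample sizes.

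**The case against.** The strongest reply is that the article never says the arms are pooled. Correlations by arm or at baseline fit its wording, and both are free of the artefact. The second aim speaks of severity, which T0 data can answer. The third is put as exploration ("explore potential neurobiological mechanisms with the help of fNIRS"), and the Discussion's language is conditional. No decision rule depends on the result, and an analysis plan that is not shown may settle the details.

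Much of this stands. A reader might infer that the protocol commits to a pooled analysis, or that the second and third aims are both compromised; the text supports neither. What does not fall away is the combination of a method without an arm term and a stated intention to interpret correlated improvements. T0 data cannot speak to improvements, and one coefficient over the whole sample is the ordinary reading of section 2.7.2.

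On size, a reader might take the 1.06 SD from step 2 as the effect on change scores and arrive at r = 0.22 with about 44% false positives at N = 66. That figure is in raw-score SD. It carries over to change scores only at ρ = 0.5, where the plan's formula needs 34 patients, not 66. At the ρ = 0 that reproduces 66, it is 0.75 SD and about 17%. Nor does a more effective treatment by itself make a spurious finding more likely: the marker must move too.

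The article also names no single fNIRS or WCST variable for this analysis. For exploratory work that is detail usually left to the analysis plan, and it is not part of this point.

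**Conclusion.** The concern holds in conditional form. If the correlations are computed over both arms on change or post-treatment scores, they cannot separate a link within arms from a treatment effect on both measures, and so cannot support the mechanism reading. Over the range examined at N = 66, the false-positive rate runs from the nominal 5%, when the marker does not respond, to about 17%, when both change scores shift by 0.75 SD.

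This rests on normal data with equal SDs, no true within-arm correlation, a two-sided test at 0.05 (the article does not state sidedness), 0.25 read as Cohen's f, and assumed marker effects. The rates are for Pearson; Spearman has no arm term either, so the same argument applies, but its rates were not computed. The consequence is confined to a secondary, exploratory analysis. It is worth correcting because the better method costs almost nothing.

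**What to change.** In section 2.7.2, state that the analysis of improvements uses changes from T0 and name the time point. Replace the plain coefficient with the partial (Pearson or rank) correlation of SHAPS change and marker change given arm. For Pearson, the same test is the marker-change coefficient in a regression of SHAPS change on marker change and arm; the two baselines can be added to that regression. Report the within-arm estimates alongside, as description, since each rests on about 33 patients (66/2). Keep unadjusted correlations for T0 only, where they can serve the second aim.

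The cost is one degree of freedom for arm (one more for each baseline added) and a change of wording. No new data, visits or patients are needed.

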Several limitations of this study should be acknowledged. Firstly, although every effort was made to maintain participant blinding, it is possible that some individuals may have inferred their intervention assignment during the trial based on their prior rTMS experience. Secondly, the study included only a 4-week follow-up period, resulting in a relatively short overall duration and limiting the evaluation of long-term efficacy. Finally, the use of fNIRS to assess brain function in this study is constrained by its limited resolution and penetration depth, which hampers precise localization of neural activity. Future research could incorporate multimodal imaging techniques, such as magnetic resonance imaging, to improve anatomical accuracy and provide deeper mechanistic insights.

In summary, if our study demonstrates that high-frequency iTBS targeting the DMPFC is a safe and effective approach for alleviating anhedonia in schizophrenia, it could offer a novel avenue for treating this symptom in affected patients.

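### The 50% correct-guess criterion is not a valid test of blinding and can contradict the chi-square comparison planned beside it

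*Protocol article*

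**What the plan says.** Section 2.7.2 (Statistical considerations) of the protocol article describes the blinding check in three sentences.

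- **Data collected:** "participants were asked at the conclusion of the treatment period to guess their group assignment (active or sham"). The guess has two options and is taken once, at the end of treatment.
- **Comparison:** "The distribution of guesses between the two groups was compared using a χ² test". The text does not say how the result is to be interpreted.
- **Criterion:** "A correct guess rate no better than chance (50%) in both groups would be considered evidence of successful blinding". This is the only statement that links a result to a conclusion about blinding.

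The article does not say how 'no better than chance' is to be judged, or which check prevails if the two disagree. The limitations paragraph of the Discussion accepts that "it is possible that some individuals may have inferred their intervention assignment during the trial based on their prior rTMS experience".

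**The concern.** Blinding is intact when the guess does not depend on the arm. That is a statement about the difference between arms, and the chi-square test addresses it. The 50% criterion instead compares each arm's correct rate with a fixed value. That rate mixes two things: how far guesses depend on the arm, and how far all participants lean towards one answer. A shared lean towards 'active', or towards 'sham', raises the correct rate in one arm and lowers it in the other without any unblinding.

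The two checks in the same paragraph can therefore point in opposite directions, and the one tied to a conclusion is the unsound one. The sham is a coil tilted by 90° (section 2.4), and the article itself concedes that some participants may infer their allocation. Readers will therefore look at the blinding statement when they judge a difference on the SHAPS.

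**Working it through.** **Inputs**
- Allocation (section 2.1): "Participants will be randomly assigned in a 1:1 ratio to receive either active or sham iTBS".
- Randomized total (section 2.7.1): "the total sample size needed for this study would be 82 participants". So 82 / 2 = 41 per arm.
- Before the dropout allowance (section 2.7.1): "We will need a sample size of 66 participants". So 66 / 2 = 33 per arm, used as a sensitivity case.
- Assumptions, not in the article: the values of g, and the meaning of 'no better than chance'. Two readings are shown. *Literal*: observed rate at most 50%. *Lenient*: not significantly above 50% by a one-sided exact binomial test at 0.05.

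The article gives no numerical result for the blinding check, so there is no figure to reproduce.

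**Step 1: algebra under intact blinding**

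Let P(guess 'active') = g in both arms.
- Correct rate, active arm = g.
- Correct rate, sham arm = 1 − g.
- Sum = 1, so both can be at or below 0.5 only if g = 0.5 exactly.

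**Step 2: a shared lean, no unblinding**

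29/41 guess 'active' in each arm.
- Active arm correct: 29/41 = 70.7%. Exact binomial against 0.5: two-sided p = 0.012, one-sided p = 0.006.
- Sham arm correct: 12/41 = 29.3%.
- Criterion: not met on either reading.
- Pearson chi-square for 29/41 against 29/41: 0, p = 1.

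**Step 3: probability that a perfectly blinded trial meets the criterion (41 per arm)**

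Literal: at most 20 of 41 correct in each arm, so P = F(20; 41, g) × F(20; 41, 1 − g), where F is the binomial distribution function.

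Lenient: the one-sided test first rejects at 27/41 (65.9%), so P = F(26; 41, g) × F(26; 41, 1 − g).

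| g | Literal | Lenient | Chi-square rejects |
|---|---|---|---|
| 0.5 | 0.500 × 0.500 = 25% | 0.970 × 0.970 = 94% | 6.0% |
| 0.6 | 0.097 × 0.903 = 8.7% | 0.725 × 0.999 = 72% | 5.5% |
| 0.7 | 0.0036 × 0.996 = 0.4% | 0.224 × 1.000 = 22% | 4.9% |

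At 33 per arm the literal figures are 25%, 10.6% and 0.8%, and the lenient ones 92%, 72% and 27%. The chi-square stays near its nominal 5% throughout.

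**Step 4: real unblinding, 60% correct in both arms (41 per arm)**

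Lenient: F(26; 41, 0.6)² = 0.725² = 53%. The criterion declares success about half the time. Literal: F(20; 41, 0.6)² = 0.097² = 0.9%. The literal reading rarely misses this case, but at the price shown in step 3.

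**Step 5: guesses depend on the arm, in the wrong direction**

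12/41 in the active arm and 29/41 in the sham arm guess 'active'.
- Correct: 12/41 = 29.3% in each arm, so the criterion is met on either reading.
- Chi-square = 14.1, p = 0.0002.
- At a true correct rate of 30% in both arms, the criterion is met 99% (literal) or almost 100% (lenient) of the time, while the chi-square rejects 97% of the time.

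**The case against.** **A sound comparison is already planned.** The chi-square gives the right answer in steps 2 and 5, and a reader of the trial report would see it. This stands, and it narrows the point: the fault is that the declared criterion is not tied to that test and can contradict it.

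**No failure rule is stated.** The article says what would count as evidence of success. It does not say that exceeding 50% in one arm means blinding failed. A reader might infer that the plan would label a well-blinded trial as failed; the text does not go that far. What can be said is that such a trial would not meet the only criterion given.

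**'Whenever guesses lean' is too strong.** A reader might infer that any lean at all breaks the criterion. That holds only on the literal reading. On the lenient one, 27/41 correct in one arm is needed, and the 25% and 9% become 94% and 72%. This stands, but at g = 0.7 even the lenient reading is met only 22% of the time, and it has the weakness in step 4.

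**The reversed pattern in step 5 is unlikely.** Nothing in the article suggests it would occur here. It shows only that the criterion does not measure dependence on the arm; the practical weight lies in steps 2 to 4.

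**Wider complaints.** A reader might also fault the absence of an early guess, a 'do not know' option, or recorded and analysed prior rTMS exposure. These are preferences or details that a condensed article may leave out. Section 2.1 mentions clinical data at baseline without itemising them, so it cannot be judged whether prior rTMS is recorded. Nor does disclosing that risk oblige the trial to exclude such patients.

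**Conclusion.** The point holds. The 50% criterion is wrong as written, on either reading:

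- **Literal:** intact blinding meets it at most about 25% of the time at 41 per arm, falling to 0.4% at g = 0.7.
- **Lenient:** intact blinding meets it 94% of the time with no lean but 22% at g = 0.7, and real unblinding with 60% correct in both arms meets it 53% of the time.

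These figures assume 41 guesses per arm, two answer options, independent participants, and the one-sided 0.05 level for the lenient reading. The values of g are illustrative; the article gives none. The algebra in step 1 depends on none of the numerical choices.

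The consequence is confined to the conclusion about blinding. The primary mixed model, the sample size and the conduct of the trial are untouched, and the documents do not support reading this as a threat to the primary analysis itself.

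**What to change.** In section 2.7.2:

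1. Delete the 50% criterion.
2. Base the blinding statement on the between-arm difference in the proportion guessing 'active', with a 95% CI, alongside the planned chi-square test.
3. Add Bang's blinding index for each arm with a 95% CI. With two answer options this is 2 × (correct rate) − 1. In step 2 it is +0.41 (active) and −0.41 (sham), which displays the shared lean openly.
4. Attach no pass/fail label. A non-significant chi-square at this sample size does not show that blinding held; the interval shows what remains compatible with the data.
5. State that a guess taken at the end of treatment cannot separate unblinding from perceived benefit.

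**Cost:** a few lines of analysis text. Only the guesses already planned are needed, so the change remains possible although recruitment was due to end in December 2025 (section 3.1). It should be fixed and dated before the allocation is revealed to the investigators.
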